### Sample size

According to Polit and Beck [42], when using ANOVA to compare the means of multiple groups, the simplest method to calculate the sample size is to estimate the ratio of the sum of squared deviations between the groups and the sum of squared deviations of the total (eta-squared, *η*2). However, when there is no experimental result of the same kind of study to base *η*2, the researcher can predict whether the study effect is large, medium, or small. According to the convention, ANOVA is used to compare the means of the smartwatch group, wristband group, and control group. The *η*2 values of large, medium, and small effects are 0.14, 0.06, and 0.01, respectively. The corresponding sample sizes of the three groups are 22, 53, and 319, and the sample size of each group is 22, 53, and 319 when *α* = 0.05 and *β* = 0.02, respectively. Because there were no suitable previous research results as the basis for calculating sample size by formula, the sample size is determined by the estimation method. Taking *α* = 0.05 and *β* = 0.02, the effect is estimated to be medium, and the number of samples in each group is 53. Considering the loss of samples and other reasons to increase the sample content by 15%, we finally included 61 cases in each group for a total of 183 subjects.

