**Methods:**

This parallel-group randomized controlled trial will be conducted in two hospitals and patients’ homes. A total of 183 adult stroke patients will be enrolled in the study and randomly assigned to three groups in a 1:1:1 ratio. The smartwatch intervention group (*n* = 61) will receive Real-time and Individualized Self-management Support (RISS) program + routine care, the wristband group (*n* = 61) will wear a fitness tracker (self-monitoring) + routine care, and the control group (*n* = 61) will receive routine stroke care. The intervention will last for 6 months. The primary outcomes are neurological function status, self-management behavior, quality of life, biochemical indicators, recurrence rate, and unplanned readmission rate. Secondary outcomes are resilience, patient activation, psychological status, and caregiver assessments. The analysis is intention-to-treat. The intervention effect will be evaluated at baseline (T0), 2 months after discharge (T1), 3 months after discharge (T2), and 6 months after discharge (T3).

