The SPSS 22.0 statistical analysis software will be used to analyze the data, and *P* < 0.05 (two-sided test) will be considered statistically significant. Count data are described by frequency/constituent ratio, and measurement data are described by mean/standard deviation according to the results of the normality test. Pearson’s chi-square test will be used to compare the count data between groups. One-way analysis of variance will be used to compare the measurement data between the three groups, and the Bonferroni method will be used for further comparison between the two groups. Repeated measures analysis of variance will be used to compare the longitudinal changes in indicators with a normal distribution. If the covariance matrix of the observed values at each time point is symmetric or spherical (Mauchly’s test, *P* ≥ 0.05), no correction will be needed. If the covariance matrix of the observed values at each time point is *P* < 0.05 (Mauchly’s test), the Greenhouse‒Geisser correction test will be used.

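### The sample-size section states β = 0.02 (98% power), but 53 per group gives about 81% power for the three-group ANOVA, so the figures match β = 0.20.

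*Protocol article*

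**What the plan says.** The Sample size section sizes the trial on a one-way comparison of three means: "ANOVA is used to compare the means of the smartwatch group, wristband group, and control group". In the absence of earlier results it uses conventional effect sizes: "The *η*2 values of large, medium, and small effects are 0.14, 0.06, and 0.01, respectively". It attaches group sizes to them, "and the sample size of each group is 22, 53, and 319 when *α* = 0.05 and *β* = 0.02, respectively", and repeats β when it makes its choice: "0.02, the effect is estimated to be medium, and the number of samples in each group is 53". An allowance for losses and other reasons follows: "increase the sample content by 15%, we finally included 61 cases in each group for a total of 183 subjects".

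For the analysis of continuous measures, the Data management and statistical analysis section plans a one-way ANOVA across the three groups, after which "the Bonferroni method will be used for further comparison between the two groups". The hypothesis, in the Study design section, compares the RISS group with the wristband group and with the control group on recurrence and quality of life.

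**The concern.** β is the probability of missing the assumed effect, so β = 0.02 promises 98% power. The listed group sizes look far too small for that. Every input to the calculation is printed, so the statement can be tested directly.

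At stake is how a non-significant result is read. Under the printed β, a medium effect would be missed about 1 time in 50. If the true figure is nearer 1 in 5, a null result says much less than the protocol implies. A second, smaller question is what the stated power refers to, since the sizing is for the overall F test while the hypothesis concerns particular pairs of groups.

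**Working it through.** **Inputs from the protocol.** Three groups allocated 1:1:1; α = 0.05; η² = 0.14, 0.06 and 0.01; n per group = 22, 53 and 319; stated β = 0.02.

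**Formula.** For a one-way ANOVA with three groups of size n, the F statistic has 2 and 3n − 3 degrees of freedom and noncentrality λ = 3n × η²/(1 − η²). Power is the probability that this noncentral F exceeds the 5% critical value of the central F.

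**Step 1: the chosen size.** η²/(1 − η²) = 0.06/0.94 = 0.0638. With n = 53, λ = 159 × 0.0638 = 10.15, with 2 and 156 degrees of freedom and critical value 3.05. Power = 81.4%, so β = 18.6%.

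**Step 2: all three listed sizes.**

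| η² | n per group stated | Power at that n | n needed for β = 0.20 | n needed for β = 0.02 |
|---|---|---|---|---|
| 0.14 | 22 | 82.5% | 21 | 40 |
| 0.06 | 53 | 81.4% | 52 | 100 |
| 0.01 | 319 | 80.0% | 319 | 625 |

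The stated sizes equal the β = 0.20 column or exceed it by one. Each is close to half of what β = 0.02 requires.

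**Step 3: could another convention rescue 53?** Using η² itself in place of η²/(1 − η²) gives 78.8%. Using α = 0.10 gives 88.7%. Neither is near 98%.

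**Step 4: power at the enrolled size.** 53 × 1.15 = 60.95, rounded to 61; 3 × 61 = 183, as stated. With all 61 per group analysed, λ = 183 × 0.0638 = 11.68 and power is 86.8%. If 15% were lost, 61 × 0.85 = 51.9, about 52 per group, and power is 80.6%.

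**Step 5: pairwise power (side note).** Two things here are assumed, not stated: that Bonferroni covers three pairs, so α = 0.05/3 = 0.0167 each, and how the three means are arranged. With f = √(0.06/0.94) = 0.2526, two patterns consistent with η² = 0.06 are:

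- RISS above two equal groups: d = 0.2526 × √4.5 = 0.536 for both RISS contrasts.
- Equally spaced means, wristband in the middle: d = 0.2526 × √6 = 0.619 against control, and half of that, 0.309, against wristband.

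Power for each contrast uses the noncentral t with 156 degrees of freedom and noncentrality d × √(53/2). Power for both contrasts comes from a 200,000-run simulation. With 53 per group:

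| Pattern of means | RISS vs wristband | RISS vs control | Both |
|---|---|---|---|
| Wristband equals control | 63% | 63% | 48% |
| Equally spaced | 21% | 78% | 20% |

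**The case against.** The strongest defence is that 0.02 is a misprint of 0.20. All three sizes fit 0.20, so the sizing was evidently done at conventional 80% power and nothing in the design is wrong. This stands as far as the design goes: 183 patients need not change. It does not remove the error, because the wrong β is printed twice and a reader has no other statement of power to go by.

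Three stronger readings are tempting, and the protocol does not support them.

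- *The 15% allowance is miscalculated.* A reader might take it as a 15% loss rate, for which 53/0.85 = 62.4, rounded up to 63, would be needed. The text describes a 15% increase in sample size, and 53 × 1.15 delivers that. It does not claim that 53 would remain after 15% loss.
- *The trial has only 48–63% power for its hypothesis.* Those two figures are not a range. One is power per contrast and the other is power to win both, and both require wristband to equal control. The protocol fixes no pattern of means and does not define success as winning both comparisons. Power for a single contrast can be lower or higher than these figures.
- *Bonferroni should be replaced.* With three groups, unadjusted pairwise tests after a significant F test would have more power, but Bonferroni is valid and that route gives up simultaneous confidence intervals. It is a choice, not a correction.

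Basing the sample size on the overall F test is a limitation that the section states openly. It is not an arithmetic error.

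**Conclusion.** The stated β is wrong. At the protocol's own inputs, 53 per group gives a type II error of about 19%, not 2%, roughly nine times the printed value (18.6/2 = 9.3). With all 61 retained it is about 13%. This conclusion rests only on the printed inputs and the standard ANOVA power formula. That 0.20 was intended is an inference, but a strong one, since all three sizes agree with it.

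The error lies in the statement of power, not in the number of patients. The pairwise figures are supplementary and conditional on an assumed mean pattern, three Bonferroni pairs, a continuous outcome and 53 evaluable per group. They say nothing about recurrence, which is binary and would be compared by chi-square test.

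**What to change.** 1. In the Sample size section, replace β = 0.02 by β = 0.20 in both places.
2. Keep 61 per group (183 in total). State that power for the overall F test at η² = 0.06 is about 81% with 53 evaluable per group, about 87% if all 61 are retained, and about 81% if 15% are lost, leaving 52.
3. Add one sentence saying that this power is for the overall F test on a continuous outcome and not for the Bonferroni pairwise comparisons or for recurrence. If pairwise power is quoted, give the assumed pattern of means and both rows of the pairwise table.

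The cost is a wording change, with no effect on enrolment or analysis. The stated power becomes less favourable. If 98% power really was intended, the evaluable size would have to be 100 per group, but nothing else in the section points that way.

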### Study interventions

Subjects in the smartwatch intervention group will receive the RISS program + routine care, subjects in the wristband group will receive exercise wristbands (Huawei Bracelet 6 FRA-B29) + routine care, and subjects in the control group will receive routine stroke care. Specific interventions for the three groups are as follows:1. Smartwatch intervention group:Build a real-time and individualized support system for stroke patients with a cloud platform as the core.

The system is composed of three parts: a data acquisition layer, a data transmission layer, and a platform service layer. (1) Data acquisition layer—a medical-grade smartwatch will be used, which has the functions of measuring blood pressure (balloon type), heart rate, and electrocardiogram patterns and screening for arteriosclerosis risk and sleep disturbances including sleep apnea, blood oxygen saturation, body temperature, Global Positioning System (GPS), and exercise state. The device has been registered as a class II medical device by the National Medical Products Administration and has good stability and accuracy. (2) Data transmission layer: the smartwatch will be connected to the patient’s personal phone, and the mobile app will be downloaded. The patient’s health data collected by the smartwatch will be transmitted to researchers via Bluetooth in real time. The app can realize family spatial data sharing so that family members can check the patient’s blood pressure and heart rate at any time, and the data in the mobile app can be transmitted to the platform service layer through web service technology. (3) Platform service layer—health data such as blood pressure, heart rate, and electrocardiogram patterns collected in real time will be uploaded to the database of the platform server and processed by the *k*-means clustering method; the calculations will be transmitted in real time to assist the medical staff of the background research team in supporting patients’ self-management. A “common problem–solution database” for stroke patients is set up in the platform. When the data monitored by the smartwatch is normal, researchers will intervene according to the problems that may occur in the routine stages of the disease and any individual problems a patient may have. When the data exceeds the warning value, the warning signal will trigger the abnormal situation processing scheme library, and the platform will push the corresponding solutions to the mobile phone of the patient and his or her family and send a warning to the medical staff, who will take measures to help the patient recover to his or her normal state as soon as possible. When the patient’s emergency reaches the alarm limit, the platform will push the first aid plan to the patient and his or her family and remind them to dial 120 and notify the medical staff about the emergency (Fig. 3).

**Fig. 3 Fig3:**
[figure not shown]
The real-time self-management support cloud platform system for stroke patients

(2) Implementation of intervention① Intervention activities before discharge

Time: the day before discharge

Location: hospital

Objective: to help subjects analyze the status of self-management, identify individual problems, formulate self-management goals together with subjects, and understand the use of smartwatches and precautions.

Content: (a) The subjects are given home self-management health guidance manuals, which include medication compliance, rehabilitation training precautions, psychological adjustment, symptom self-detection, diet adjustment, life, work and rest, regular medication, and regular follow-ups, and they are also given discharge guidance. The main content teaches compliance with the doctor’s advice after discharge, health lifestyle education, and self-management status analysis. At the same time, the subjects will keep home diaries. Evaluating subjects before discharge to determine their self-management-related problems in the four domains of environmental, psychosocial, physiological, and health-related behaviors; and to formulate health goals after discharge with the subjects/caregivers. (b) Demonstrate the use of smartwatches, explain the precautions in the use of smartwatches, and teach the subjects to use smartwatches skillfully.

②Intervention activities after discharge

Time: the intervention will last for 6 months after discharge, and the intervention is conducted twice a week in the first 2 weeks at home, once online, and once offline. The intervention will be conducted once a week from the 3rd to the 8th week, online and offline are combined, and patients are followed up at the end of 2 months, 3 months, and 6 months after discharge.

Location: home

Objective: to provide targeted and individualized interventions for subjects’ problems and reduce complications.

Content:aDeveloping a common problem–solution library for stroke patients’ self-management.

Prior to the intervention, a cross-sectional survey and semi-structured interview will be conducted among stroke patients in transition to form a common problem set on self-management. Based on the set, a common problem–solution library (CPS) for stroke patients will be established according to various stroke guidelines. We will invite 8–12 experts to evaluate the initial version of the CPS and plan to finalize the revised version through 2–3 rounds of expert consultation.

bDeveloping an individualized problem–solution library for stroke patients’ self-management.

During the intervention period, for patients in the intervention group, objective data (blood pressure, heart rate, electrocardiogram, and other objective data collected by smartwatch) and subjective data (semi-structured interviews with patients, caregivers, medical staff, community workers, and other relevant people who may affect patients’ self-management behavior) will be analyzed before each intervention to identify individual problems of each patient. Then, according to the CPS and combined with the patient’s own characteristics, the medical staff will carry out individualized interventions on the problems of each patient according to the five steps of the RISS program, namely, describing the problem, establishing feasibility goals, exploring patients’ advantages and providing individualized interventions, giving feedback, and evaluating progress (Supplementary file 1). After completion of each intervention, the medical staff will record the problems, measures taken, and effect analysis of each patient in detail in the form of “disease management log” on the administrator end of the cloud platform. After 8 weeks of about 10 consecutive assessments and interventions, the problems existing in the transitional period of patients might be saturated, and the solution library for these problems is also established, which is the individualized problem–solution library (IPS) for self-management.

After the completion of the last intervention, we will send the CPS and the IPS to each patient in the form of a guidance manual and assist patients to make a self-management supervision sheet, so that patients can identify their problems in self-management and individualized solutions. It can point out the direction for the long-term maintenance and continuous improvement of good self-management behavior of patients in the future.2. Wristband group

The subjects in the bracelet group will wear exercise wristbands that can record heart rate, sleep, blood oxygen, and exercise in real time, and the subjects will conduct self-testing at home. At the same time, the subjects will be given routine discharge care, that is, telephone follow-up twice in the first week and the fourth week after discharge. The content will include the implementation of the discharge doctor’s advice, inquiry of physical function recovery, health advice for common problems, and rehabilitation guidance.3. Control group

Subjects in the control group will receive routine discharge care, that is, telephone follow-up twice in the first week and the fourth week after discharge, which will include the implementation of the discharge doctor’s advice, inquiries about physical function recovery, health advice for common problems, and rehabilitation guidance.

### Evaluation methods

An assessor-blind method is used; that is, questionnaire collectors are research assistants who are trained in the use of measurement tools but are blinded to the grouping of study subjects. The intervention effects of the three groups of patients will be measured at baseline and 2 months, 3 months, and 6 months after discharge. The evaluation content includes questionnaire surveys and biochemical index measurements. Baseline data (during hospitalization) collection: Patients will complete the assessment at the nurses’ station. Follow-up data (after discharge from the hospital) will be collected as follows: The research assistant will visit the patient at home for data collection. Patients will complete the assessment independently, but those with reading difficulties, visual impairment, or handwriting difficulties will be instructed to complete the questionnaire as each item is read to them in neutral, noncryptic language. After the evaluation, the researchers will check whether the evaluation is complete. If there are missing items, patients will complete the items on the spot and return the evaluation for verification again. Any doubts about the content will be verified with the patient on the spot. Upon completion of data collection at each follow-up time point, each study patient will receive a gift for participating in the study. Basic demographic data will be collected at baseline, including age, sex, ethnicity, education level, marital status, job status, family status, and medical condition.1. Primary outcome (for patients)

The primary outcomes are neurological function status, self-management behavior, quality of life, biochemical indicators, recurrence rate, and unplanned readmission rate.

Neurological status

The National Institutes of Health Stroke Scale (NIHSS) is the most common stroke evaluation index in the world. It covers the anterior and posterior circulation of the brain, including consciousness, movement, sensation, speech, and visual field, with a total of 15 items. NIHSS scores range from 0 to 42, with higher scores indicating more severe neurological impairment [43]. Cai Yefeng et al. introduced the NIHSS in China to conduct a multicenter and large sample test, and the results showed that the Chinese version of the NIHSS had good reliability, validity, and sensitivity [44].

The Modified Barthel Index (MBI) will be used to assess the patient’s ability to perform ADLs. The scale contains 10 items: eating, grooming (washing face, brushing hair, brushing teeth, shaving), bathing, dressing (unfastening buttons, zipping zippers, putting on shoes and socks), bowel and urine control, toileting, bed-chair transfer, moving on the ground, and walking up and down stairs [45]. Each item is rated on a 1–5 scale as completely dependent, needing a lot of help, needing moderate help, needing little help, and being completely independent. Normal is 100 points, with a score of 91–99 indicating mild dependence; 61–90, moderate dysfunction; 21–60, severe dysfunction; and 0–20 points, completely dependent. The Chinese version has good reliability and validity [46].

(2) Self-management behavior: The Stroke Self-management Behavior Rating Scale (SSBR) will be used to measure the level of self-management behavior of stroke patients. The scale covers 7 dimensions: disease management, medication management, diet management, daily life management, emotional management, social function and interpersonal management, and rehabilitation exercise management, with a total of 51 items. Each item is scored from 1 to 5 points, and the total score of the scale ranges from 51 to 255. The higher the score, the better the self-management behavior of the patients. The Cronbach’s *α* coefficient is 0.847, and the construct validity is 0.761. The scale has been widely used in China and has good reliability and validity [47].(3) Quality of life: The 12-item Medical Outcomes Study Short Form Health Survey version 2.0 (SF-12 v2) developed by Boston Health Research Institute will be used to measure the quality of life of patients. It has eight dimensions: general health (GH), physical functioning (PF), role physical (RP), bodily pain (BP), vitality (VT), social functioning (SF), role emotional (RE), and mental health (MH), with a total of 12 items. The total score of the GH, PF, RP, and BP dimensions is the physical component summary (PCS). The total score of the SF, RE, MH, and VT dimensions is the mental component summary (MCS), and the standardized score of each part ranges from 0 to 100. The higher the score, the better the quality of life of the patient. The total Cronbach’s *α* coefficient of the Chinese version of the questionnaire is 0.84, and Cronbach’s *α* coefficient of each dimension is greater than 0.70 [48].(4) Recurrence rate: In China, the recurrence rates of stroke patients at 3 months, 6 months, and 1 year are 12.9%, 16.0%, and 17.7%, respectively [49]. The mortality and disability rate after the recurrence of stroke will be higher, which creates a more serious burden for patients and their families. Therefore, the recurrence rate of stroke after discharge will be used as one of the evaluation indicators in this study.(5) Biochemical indicators: Blood glucose and blood pressure are important risk factors for stroke recurrence [50, 51]. In this study, the blood glucose and blood pressure of patients will be measured by a stable glucose meter (Sinocare Anzhun) and an Omron sphygmomanometer (Sinocare BA-802).(6) Unplanned readmissions: Unplanned readmissions for stroke patients are defined as unplanned readmissions to the department of neurology of a hospital for similar conditions within 30 days or less from the date of last discharge to the date of readmission. It is calculated using the following formula [52]: unplanned readmission rate = number of unplanned readmissions/total number of discharges in the group. The Health Commission of China considers unplanned readmission of stroke patients as one of the sensitive indicators of hospital return and an important indicator to evaluate the quality of hospital care [53].

2. Secondary outcomes (for the patient)

The secondary outcomes include resilience, patient activation, psychological status, and main caregiver evaluation indicators, including caregiver burden, family resilience, and social resource utilization.

(1) Resilience: The 10-item Connor and Davidson Resilience Scale (CD-RISC 10) contains a total of 10 items, which are divided into two dimensions: strength and resilience. The total score of the scale is the sum of the scores of each item. The higher score indicates a higher level of resilience [54]. Cronbach’s *α* of the Chinese version of the scale is 0. 922 [55].(2) Patient activation: The patient activation scale consists of 13 items, and the scores range from 0 to 100 points using Lister’s 5-point scale. The higher the score, the higher the patient activation level [56]. Cronbach’s *α* coefficient of the Chinese version of the scale is 0.88 [57].(3) Social Support: The Multidimensional Scale of Perceived Social Support (MSPSS) consists of three dimensions: significant other, family, and friends, with a total of 12 items. The scores range from 12 to 84, with higher scores indicating more social support [58]. Cronbach’s *α* coefficient of the Chinese version is 0.896 [59].(4) Depression: The Patient Health Questionnaire-9 (PHQ-9) contains 9 entries, each with a score of 0–3. The questionnaire is assessed according to the sum of items, and the higher the score, the higher the degree of depression [60]. This questionnaire has been widely used in the world, and the Chinese version of Cronbach’s *α* coefficient is 0.743 [61].

3. Secondary outcomes (for informal caregivers)(1) Caregiver burden: The Caregiver Burden Scale consists of two dimensions, individual burden and responsibility burden, with a total of 22 items. The higher the score, the heavier the burden of caregivers [62]. Cronbach’s alpha coefficient of the Chinese version of the scale is 0.96 [63].(2) Family resilience: The Family Resilience Scale is used to assess resilience within the family. The scale includes three dimensions of commitment, challenge, and control, with a total of 20 items. Lister’s 4-point scale will be used, and higher scores indicate better family resilience [64]. Cronbach’s *α* coefficient of the Chinese version of the scale is 0.803 [65].(3) Social resource utilization: The chronic illness resource scale was developed by Glasgow et al. [66], and Yao Xiaoyue et al. [67] revised it. The scale is used to measure the support of patients from seven resources, such as personal, health management team, family/friends, community/neighborhood, media/policy, and workplace, for common self-management behaviors of patients, such as diet, exercise, and medication management behaviors. Based on this scale, we will conduct interviews on the availability of different resource levels.

4. Substudy

As a substudy of this trial, we will use cost-effectiveness analysis to evaluate the cost and effectiveness of transition management of stroke patients based on wearable devices. Health economics indexes are evaluated by cost, cost-effectiveness analysis, and sensitivity analysis. The cost-effectiveness of the smartwatch group, control group, and bracelet group are compared with each other to provide a reference for realizing the optimal allocation of medical resources.

